# Protocol for visual-acoustic intervention with service delivery in-person and via telepractice (VISIT) non-inferiority trial for residual speech sound disorder

**DOI:** 10.1186/s12887-024-05364-z

**Published:** 2025-01-27

**Keywords:** Speech sound disorder, Randomized controlled trial, Biofeedback, Telepractice

## Abstract

**Background:**

Residual speech sound disorder (RSSD) is a high-prevalence condition that negatively impacts social and academic participation. Telepractice service delivery has the potential to expand access to technology-enhanced intervention methods that can help remediate RSSD, but it is not known whether remote service delivery is associated with a reduction in the efficacy of these methods. This project will systematically measure the outcomes of visual-acoustic biofeedback intervention when delivered in-person or online.

**Methods/design:**

This project, *Visual-acoustic Intervention with Service delivery In-person and via Telepractice (VISIT)*, aims to treat 76 children in a parallel randomized controlled clinical trial in which children with RSSD will receive visual-acoustic biofeedback treatment either in person or via telepractice. Eligible children will be speakers of American English aged 9–17 years who exhibit RSSD affecting /ɹ/ but otherwise show cognitive-linguistic and hearing abilities within the typical range. All participants will receive twenty sessions of visual-acoustic biofeedback; they will be randomized, with stratification by pre-treatment speech production ability and site, to complete their treatment sessions either in the laboratory setting or at home via telepractice. For the primary outcome measure, blinded listeners will evaluate changes in the perceived accuracy of /ɹ/ production after the end of treatment.

**Discussion:**

By comparing outcomes in children randomized to receive a standard course of biofeedback treatment either via telepractice or in-person, this study will provide evidence-based guidance for clinicians seeking flexible service delivery options for a challenging and prevalent condition.

**Trial registration:**

ClinicalTrials.gov identifier NCT06517225, 07/23/2024. URL: https://clinicaltrials.gov/study/NCT06517225.

**Supplementary Information:**

The online version contains supplementary material available at 10.1186/s12887-024-05364-z.

## Background

Children with speech sound disorder (SSD) exhibit atypical speech patterns that negatively affect intelligibility, posing a barrier to participation in social and academic settings [1]. Delayed speech development typically resolves by 8–9 years old, but 2–5% of speakers experience residual speech sound disorder (RSSD) that persists through adolescence or even adulthood [2–4]. RSSD is often associated with an increased incidence of peer difficulties or bullying [5–7], and the impact on educational, occupational, and mental health outcomes may be lifelong [1, 8, 9]. RSSD is considered particularly challenging to remediate, and speech-language pathologists (SLPs) have called on the research community to develop improved treatment methods for this diagnosis [10]. Residual errors affecting rhotic sounds in North American English (which include /ɹ/ as in the start of the word *read* and /ɝ/ as in the word *her*) are widely regarded as one of the most common and challenging forms of RSSD [10]. To ensure a relatively homogeneous population, this study focuses on individuals with RSSD affecting rhotic sounds.

Recent evidence suggests that visual biofeedback, which uses instrumentation to provide real-time information about aspects of speech that are typically outside the speaker’s conscious control [11], can be used to enhance intervention for RSSD and other speech disorders. Visual biofeedback can incorporate various technologies. The focus in this study is on *visual-acoustic biofeedback*, in which a microphone and software are used to generate a real-time display of the acoustic signal of speech. In the present case, a real-time Linear Predictive Coding (LPC) spectrum is used to represent the resonant frequencies of the vocal tract, or formants. The learner views a model or template representing the formant pattern for correct productions of the target sound and is encouraged to adjust their own output to match the template in the real-time visual display.

Several small-scale studies have documented positive outcomes from visual-acoustic biofeedback treatment in individuals who previously showed minimal, if any, improvement with traditional forms of intervention. (Traditional treatment for RSSD generally involves providing auditory models and verbal descriptions of correct articulator placement, then cueing repetitive motor practice.) One study initially provided traditional motor-based treatment to 11 children with RSSD affecting rhotics, then transitioned to a phase of visual-acoustic biofeedback treatment in a staggered fashion [12]. Only two participants showed a significant response to the initial phase of treatment, while six additional participants showed significant improvements in /ɹ/ production after the transition to biofeedback treatment. Another single-case experimental study of 11 children found a significant interaction between treatment condition and order, suggesting that visual-acoustic biofeedback followed by traditional motor-based treatment yielded significantly larger effect sizes compared to the same treatments provided in the reverse order [13]. Finally, in a single-case randomization study providing both traditional treatment and visual-acoustic biofeedback to seven participants [14], three participants were observed to exhibit a statistically significant advantage for visual-acoustic biofeedback over traditional treatment, and none were found to show a significant advantage in the opposite direction. While these small-scale studies have reported promising evidence, a well-powered randomized controlled trial comparing treatment with and without visual biofeedback is needed to provide a high-quality evidence base to guide clinical decision-making. An earlier study aiming to fill this need was preregistered by our team [15] and is currently in the final stages of data collection.

Despite growing evidence of efficacy, real-world adoption of biofeedback remains limited by barriers such as equipment costs and the need for specialized training. Previous research has suggested that delivery of speech-language services via online telepractice may enable greater specialization among SLPs (e.g., for low-incidence conditions such as cleft lip/palate [16]) because recruitment of clients is not geographically limited. If visual-acoustic biofeedback intervention remains effective when delivered in the telepractice context, remote service delivery could represent a valuable means to provide access to biofeedback services to children with RSSD.

In telepractice delivery of speech services, patients are connected with an SLP for diagnosis and treatment over remote conferencing software. Telepractice has a long history in the SLP profession, where it plays an essential role in providing access to certified SLPs for rural and underserved communities. Adoption of telepractice has been increasing for decades as clients and clinicians recognize its potential for greater flexibility and efficiency (e.g [17]). Periods of confinement during the COVID-19 pandemic saw an explosive increase in SLP adoption of telepractice, and many users who tried telepractice for the first time during the pandemic may continue to opt for this approach due to its convenience [18, 19].

A 2017 systematic review on telepractice [20] reported “limited but promising evidence” that telepractice treatment for speech and language can yield effects comparable to in-person treatment. Positive client and parent satisfaction outcomes have also been documented for pediatric and adult speech therapy [21–23]. By contrast, a 2020 systematic review suggested that treatment for SSD via telepractice may yield smaller effect sizes than in-person treatment [24]. Both the 2017 and 2020 studies covered only a small number of studies (*n* = 7 and *n* = 10, respectively), many with limitations such as small sample sizes or retrospective data collection. Thus, it is not well-established if treatment for SSD is equally effective across service delivery models. Because telepractice is advantageous for other reasons, this is an appropriate context to use *non-inferiority trial* methodology [25] to assess whether any reduction in efficacy exceeds a predefined maximum acceptable difference. In the realm of communication disorders, similar reasoning has motivated non-inferiority trials on telepractice versus in-person treatment for aphasia [26], hypokinetic dysarthria [27, 28], and stuttering [29].

Prior to our research team’s efforts leading up to this preregistered trial, no published work has investigated the efficacy of SSD telepractice with visual-121 acoustic biofeedback intervention. During COVID-19 closures, we conducted a pilot study in which seven school-age participants with RSSD received 10 sessions each of traditional and visual-acoustic biofeedback treatment delivered online [30]. Clinically significant gains were exhibited by 5 of 7 participants, supporting the feasibility of visual-acoustic biofeedback treatment via telepractice. We also executed a single-case experimental study in which four children with RSSD received eight sessions each of traditional and visual-acoustic biofeedback treatment via telepractice in a randomized order [31]. Blinded listeners’ perceptual ratings of /ɹ/ word probes indicated that all four participants responded to the combined treatment package with moderate to large effect sizes. No previous research has systematically measured the effects of visual-acoustic biofeedback treatment delivered with identical procedures online and in-person, as we propose to do.

This study will randomly assign *n* = 76 children to receive a standard course of biofeedback intervention delivered in-person or via telepractice, measuring progress with blinded listeners’ ratings of untreated words produced before and after treatment. We hypothesize that biofeedback treatment delivery via telepractice will not be associated with a reduction in efficacy that exceeds a maximum acceptable value determined a priori. We will also administer a survey before and after treatment to assess changes in participants’ socio-emotional well-being, as well as participants’ and caregivers’ satisfaction with the therapy experience.

## Methods and design

Visual-acoustic Intervention with Service delivery In-person and via Telepractice (VISIT) is a parallel-group prospective randomized controlled non-inferiority trial measuring the efficacy of visual-acoustic biofeedback intervention for RSSD affecting /ɹ/ when delivered online versus in-person. All participants will receive visual-acoustic biofeedback intervention following a standard protocol and schedule; they will be randomly assigned to receive this intervention either in the laboratory setting or via online telepractice. Participant allocation in each group will be stratified by pre-treatment severity, since previous research has identified this variable as an important indicator of subsequent treatment response. Finally, allocation will additionally be stratified by site (Montclair, New Jersey; Syracuse, New York). Although not all participants will be physically present at their allocated site during treatment delivery, they must reside close enough to their study site to be able to participate in-person if randomized to that condition. They will also interact with a site-specific study team, which could potentially be relevant for study outcomes.

We plan to enroll a total of 76 children with RSSD. The power analysis to determine this sample size was based on a comparison of 12 participants from a previous study who received visual-acoustic biofeedback treatment in the in-person setting and 11 participants who received a comparable duration of visual-acoustic biofeedback treatment via telepractice. The participants seen in person had an average change score of 39.8% points (standard deviation = 25.8% points) and the participants seen online had an average change score of 36.8% points (standard deviation = 22.6% points). The population standard deviation of the outcome, after controlling for effects of clinician and baseline accuracy, was estimated at 18% points. Using the formula from Flight & Julious 2016 [32], the sample size of 38 participants per group was computed to achieve 80% power for an alpha level of 5%, assuming the non-inferiority margin delta derived as described under *Data analysis plan*. Power analysis was conducted using an online power calculator for non-inferiority trials [33].

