### Data analysis plan

The first statistical consideration for this study is the value of the margin delta (Δ), which represents the maximum acceptable loss of effect for an alternative treatment relative to an established one in a non-inferiority trial. Previous literature has suggested that delta may be defined as “less than the minimum difference of clinical interest (i.e., the minimum clinically important difference; MCID)” [28, 57]. We defined the MCID with reference to a meta-analysis of eleven single-case experimental studies of biofeedback intervention for RSSD previously published by our team [58]. In this meta-analysis, we generated de-identified plots of participants’ accuracy before and after treatment, based on perceptual ratings aggregated over blinded listeners. Three experienced researchers visually inspected these plots and reached a consensus judgment classifying each participant as responding or failing to respond to treatment. This “gold standard” binary classification was then used to compute sensitivity, specificity, and combined sensitivity-specificity for various cutoff values. ROC curve analysis revealed that a raw mean difference of 13.9% points represented the optimal cutoff between responder and non-responder categories (optimal combined sensitivity-specificity using Youden’s J). We adopt this cutoff value as the MCID. However, it is recommended that Δ be set to a value less than the MCID. Previous non-inferiority trials in the speech context have considered different values, including half of the MCID [27] or 75% of the MCID [28]. Based on the argument that high variability in response to speech treatment may lead to large confidence intervals [28], we will set our value of delta to 75% of the MCID, or 10.4% points.

The primary statistical model described below will be fit twice, once following the intention-to-treat principle, with imputed scores generated for cases of attrition, and once in an adjusted per-protocol analysis; see below for additional detail. Assessment of outcomes following both approaches is recommended for non-inferiority trials [25]. If the lower bound of the 95% confidence interval centered on the observed difference falls above the noninferiority margin of -10.4 in both models, we will conclude that noninferiority has been established.

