A second limitation of the non-inferiority design is the potential for non-adherence to the proposed treatment package to influence the conclusions of the study. In our research, the most common form of non-adherence is early study termination. If the types of study participants who terminate early in one condition are different from those that terminate early in the other, the intention-to-treat analysis might provide an overly optimistic assessment regarding non-inferiority. However, if these differences are explainable by our observed covariates, our adjusted per-protocol estimate could help remedy this situation. In accordance with recommendations for non-inferiority studies, we intend to report the results of the VISIT trial using both intention-to-treat and per-protocol analyses. For a strong conclusion of non-inferiority, both methods must show no difference between the treatment conditions exceeding the margin Δ. The US Food and Drug Administration recommends “close examination” of results where a discrepancy is observed between the intention-to-treat and per-protocol analyses. For example, consider a hypothetical scenario where the true effect size of treatment is smaller in the online condition than the in-person condition, but attrition is higher in the in-person condition, which could arise if participants find it more challenging to comply with the prescribed treatment schedule when visits are in-person. This could manifest as a difference in outcomes between the intention-to-treat analysis and the per-protocol analysis, with the latter showing a difference between treatment conditions and the former showing none. While such a finding would not support a strong conclusion of non-inferiority, it could still provide valuable information about real-world strengths and limitations of different service delivery methods. The inclusion of such results in the evidence base could help clinicians and clients make an informed decision based on their own personal values and needs.

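### The stated 80% power is for a single one-sided 5% test with no true difference and no dropout, not for the trial's own rule that two analyses must both clear a 95% confidence bound

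*Protocol article*

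**What the plan says.** Methods and design sets enrolment: "We plan to enroll a total of 76 children with RSSD". The same paragraph says that "the sample size of 38 participants per group was computed to achieve 80% power for an alpha level of 5" per cent. It gives an SD of 18 points, adjusted for clinician and baseline accuracy. It also reports the earlier data on which the calculation is said to rest: 12 children treated in person with a mean change of 39.8 (SD 25.8), while "the participants seen online had an average change score of 36.8% points" (11 children, SD 22.6). It states no assumed true difference, no attrition allowance and no sidedness for alpha.

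The Data analysis plan sets the margin at 10.4 points and gives the decision rule: "If the lower bound of the 95% confidence interval centered on the observed difference falls above the noninferiority margin" of -10.4 in both the intention-to-treat and the adjusted per-protocol model, non-inferiority is concluded. The per-protocol set consists of those who stayed in the trial and completed every assessment. Potential limitations repeats the double requirement: "For a strong conclusion of non-inferiority, both methods must show no difference between the treatment conditions exceeding the margin". On dropout it says: "In our research, the most common form of non-adherence is early study termination". No rate is given.

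**The concern.** A power figure is useful only if it describes the rule by which the trial will be judged. Here the calculation covers one test on all 76 children, while the rule covers two analyses, one of which loses every child who does not complete. The alpha in the calculation also appears to be one-sided 5%. A 95% interval centred on the estimate is most naturally read as two-sided, which makes the test one-sided 2.5%.

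All of these differences work in the same direction. If telepractice is truly no worse, the chance that the trial will show it is lower than the reader is told. A miss is then more likely than advertised, and readers may take it as a sign that telepractice is inferior.

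**Working it through.** **Inputs.** Margin 10.4 (Data analysis plan). SD 18, 38 per group, power 80% and alpha 5% (Methods and design). Attrition is not given; 10% and 20% are assumed here. Differences are written as the telepractice deficit d.

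**1. Reproducing the stated figure.** n per group = 2 × [SD × (z₁₋α + z₀.₈₀) / (10.4 − d)]². With d = 0 and one-sided 5%: 2 × [18 × (1.645 + 0.842) / 10.4]² = 37.04, rounded up to 38. The other combinations do not give 38:

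| One-sided alpha | d | n per group |
|---|---|---|
| 5% | 0 | 38 |
| 2.5% | 0 | 48 |
| 5% | 3.0 | 74 |
| 2.5% | 3.0 | 93 |

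Allowing for dropout by dividing 38 by (1 − rate) would give 43 at 10% and 48 at 20%. Enrolment is 76 = 2 × 38, so no allowance was made.

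**2. Power of one analysis, 38 per group, no attrition.** The standard error is 18 × √(2/38) = 4.13. The standardised distance to the margin is 10.4/4.13 = 2.52 at d = 0 and 7.4/4.13 = 1.79 at d = 3.0.

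| d | One-sided 5% | Two-sided 95% CI |
|---|---|---|
| 0 | 80.2% | 70.0% |
| 3.0 | 55.2% | 42.4% |

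These are noncentral t values. The normal approximation gives 80.9%, 71.2%, 55.8% and 43.3%.

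**3. Attrition, then both analyses, at d = 0 (normal approximation).** The per-protocol set has 38 × 0.9 = 34.2 or 38 × 0.8 = 30.4 children per group. It is treated as a random subset of the full set, so the two test statistics have correlation √(1 − rate). The intention-to-treat analysis is assumed to keep the information of 38 per group.

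| Assumed attrition | Alpha basis | Per-protocol alone | Both pass |
|---|---|---|---|
| 10% | one-sided 5% | 77.2% | 75.1% |
| 20% | one-sided 5% | 72.8% | 70.4% |
| 10% | two-sided 95% CI | 66.6% | 64.0% |
| 20% | two-sided 95% CI | 61.5% | 58.6% |

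**4. What each element costs at d = 0.** Reading the interval as two-sided costs about 10 points (80.2 to 70.0). At one-sided 5%, attrition of 10–20% costs about 4 to 8 points (80.9 to 77.2 or 72.8), and requiring both analyses costs about 2 more.

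**5. Precision of the earlier difference.** 39.8 − 36.8 = 3.0, with standard error √(25.8²/12 + 22.6²/11) = 10.1. With 21 degrees of freedom (multiplier 2.08), the interval for telepractice minus in-person is about -24 to +18.

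**The case against.** The sample-size arithmetic is correct, and a zero true difference is a conventional planning assumption in a non-inferiority trial. The article says that the calculation was based on the earlier comparison, but never that the 3.0-point gap was the planning value. All of this stands. The fault is that the assumption is unstated and that the power shown is not the power of the decision rule.

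A reader might infer from 39.8 and 36.8 that telepractice has been shown to be worse. The documents do not support that. There were 12 and 11 children, no randomised comparison is described, and the standard error is over three times the difference. The 3.0 is also a raw difference, while 18 is an adjusted SD; the adjusted difference is not reported and could be larger, smaller or reversed. The figures at 3.0 are therefore a sensitivity case only.

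The attrition rates are assumptions, since the article gives none. It also invites dropouts back for follow-up and imputes the rest, so losses fall mainly on the per-protocol analysis. The calculation allows for this by leaving the intention-to-treat analysis at full information.

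Finally, the largest single loss at zero difference comes from the sidedness of alpha, which the article leaves open. If the 95% bound is meant as one-sided, that loss disappears. Results are therefore shown on both readings.

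**Conclusion.** The point holds as a mismatch between the stated power and the success rule. At a true difference of zero, 80% applies to one analysis at one-sided 5% without dropout, and becomes 70% if the 95% interval is two-sided. With an assumed 10–20% attrition and both analyses required, power is about 75–70% at one-sided 5% and 64–59% under a two-sided 95% interval. These joint figures assume that completers are a random subset, that imputation costs the intention-to-treat analysis no information, and that the inverse-probability weights cost no precision.

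A true deficit of 3.0 points, which lies inside the margin, would give 55% or 42% for one analysis without attrition. A reader might conclude that the trial is more likely to fail than to succeed. That does not follow: for a single analysis it is true only under the two-sided reading, and only if a deficit of that size is real, which the earlier data cannot establish.

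**What to change.** Keep 76 children. In the power paragraph, state the assumed true difference, the assumed attrition and whether alpha is one- or two-sided. Then give power for the rule actually used, with both analyses clearing the 95% bound, at a true difference of zero. Add a small deficit such as -3.0, labelled as a sensitivity case.

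On interpretation, it is enough to say that a lower bound below -10.4 does not by itself show inferiority, and that the result will be read from where the whole interval lies relative to -10.4 and 0. A blanket rule calling every such result inconclusive would go too far, because an interval wholly below -10.4 would be evidence of inferiority.

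The cost is a few sentences or a small table, with no change to enrolment, analyses or decision rule. The downside is that the stated power becomes less favourable.

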In the intention-to-treat analysis, we will impute an outcome for participants who drop out of the study and are lost to follow-up based on data from the individuals who have complete data and are in the same treatment assignment. In the per-protocol analysis, we will attempt to estimate the effect of telehealth versus in-person treatment only for those in the sample who remained in the trial and completed all assessments. Because estimates of this effect can be biased due to systematic differences that arise when focusing on this non-random sample from the trial, we will perform an *adjusted* per-protocol analysis using inverse probability of treatment weighting, following recommendations from recent methodological research [59, 60].

Our primary outcome measure of interest is change in perceptually rated accuracy of /ɹ/ sounds from pre- to post-treatment, with perceptual ratings of pre- and post-treatment probes obtained from blinded listeners as described above. We will compute this change score for all participants and will use a linear model with a fixed effect of group to compute the 95% confidence interval around the difference in change scores between groups. The in-person group will be treated as the reference level, so that a negative value indicates smaller gains when treatment is delivered via telepractice versus in-person. The model will also control for the randomization strata of site and baseline severity group (less stimulable versus more stimulable), as well as baseline accuracy as a continuous predictor. Lastly, we do not plan to include a fixed effect of age because our previous research has not supported such an effect (e.g [61]). However, we will test for a correlation between age and treatment outcomes and if a statistically significant correlation is present, we will include age as a controlled covariate.

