A secondary analysis will report pre- to post-treatment changes on the 11-item survey assessing the social, emotional, and academic consequences of RSSD that will be administered to participants and their parents both before and after the course of treatment. We will model impact score (as defined in [5]) as the outcome variable with fixed effects of time, treatment group, and the time by treatment group interaction, as well as clinician and initial accuracy level. Likelihood ratio tests will be used to assess the significance of fixed effects and interactions in the final model. A significant effect of time would suggest a change in the perceived impact of RSSD over the course of treatment, while a significant interaction between time and treatment group could indicate a difference in the magnitude of the change in perceived impact across treatment conditions.

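### The SD of 18 behind the sample size is adjusted for clinician, but the primary model has no clinician term, so the stated 80% power does not belong to the planned analysis

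*Protocol article*

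**What the plan says.** Three places in the protocol article bear on this.

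- **Methods and design, sample size.** The pilot comparison used 12 children treated in person and 11 treated online. For the first group, "The participants seen in person had an average change score of 39.8% points (standard deviation = 25.8% points"); for the second, "the participants seen online had an average change score of 36.8% points (standard deviation = 22.6% points"). The article then moves to an adjusted figure: "The population standard deviation of the outcome, after controlling for effects of clinician and baseline accuracy, was estimated at 18% points". On that basis "the sample size of 38 participants per group was computed to achieve 80% power for an alpha level of 5" percent, with the margin taken from the Data analysis plan, where "we will set our value of delta to 75% of the MCID, or 10.4% points".
- **Data analysis plan, primary model.** A linear model on the change score has a fixed effect of group. On covariates, "The model will also control for the randomization strata of site and baseline severity group", together with baseline accuracy as a continuous predictor. Age enters only if it proves to be correlated with outcome. Clinician is not listed.
- **Data analysis plan, secondary survey model.** Besides time, group and their interaction, this model has further terms: "as well as clinician and initial accuracy level".

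**The concern.** A sample size based on an adjusted SD is valid for an analysis that makes the same adjustment, or one that removes at least as much variance. Here the planning SD takes out clinician and baseline accuracy, while the primary model takes out baseline accuracy, site and stimulability group. The two sets share only baseline accuracy.

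The unadjusted pilot SDs are well above 18, so the adjustment does a great deal of work in the calculation. If a material part of that work was done by clinician, and the primary model does not recover it through its other terms, the confidence interval for the group difference will be wider than the sample size assumed. In a non-inferiority trial a wider interval makes it more likely that a telepractice service that is truly no worse fails to be shown so.

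This is not a detail left to a separate analysis plan. The article states both the covariates behind the planning SD and those in the primary model, and the two lists differ.

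**Working it through.** **Inputs.** From Methods and design: pilot SDs 25.8 (n = 12) and 22.6 (n = 11), adjusted SD 18, 38 per group, 80% power, alpha 5%. From the Data analysis plan: margin 10.4 and the primary-model covariates. Assumption: true difference 0.

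**Step 1. Reproduce the plan's figure.** With one-sided alpha 5%:

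n per group = 2 × [SD × (1.645 + 0.842) / margin]² = 2 × [18 × 2.487 / 10.4]² ≈ 37.0

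The noncentral t calculation needs 38 and gives 80.2% power there. So 38 is reproduced, and it depends directly on the 18. Using the observed 3-point pilot difference, or one-sided 2.5%, does not reproduce it (74 and 48 per group respectively).

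**Step 2. How much variance the adjustment removed.**

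Pooled raw SD = √[(11 × 25.8² + 10 × 22.6²) / 21] = √591.9 = 24.3

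Share removed = 1 − 18² / 24.33² = 1 − 324 / 591.9 = 0.45

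Clinician and baseline accuracy together removed about 45% of the variance. The article does not report how that divides between them.

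**Step 3. Power at other residual SDs.** Standard error = SD × √(2/38) and noncentrality = 10.4 / standard error. The test is one-sided 5% on 71 degrees of freedom (76 children less intercept, group, site, stimulability and baseline accuracy).

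| Residual SD | Standard error | Noncentrality | Power |
|---|---|---|---|
| 18 | 4.13 | 2.52 | 80% |
| 20 | 4.59 | 2.27 | 73% |
| 22 | 5.05 | 2.06 | 65% |
| 24.3 (raw, extreme case) | 5.58 | 1.86 | 58% |

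**Step 4. What share of the removed variance leads where.** If clinician supplied a fraction s of the removed variance and nothing in the primary model recovered it, residual SD = √[324 + s × (591.9 − 324)].

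- s = 0.25: √391.0 = 19.8, power 73%.
- s = 0.50: √458.0 = 21.4, power 67%.

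These values of s are assumptions, since the article gives none.

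**Step 5. What would cancel the loss.** At s = 0.25, site and stimulability together would have to explain 1 − 324 / 391.0 = 17% of the remaining variance to bring the SD back to 18.

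**The case against.** The strongest reply is that the primary model drops one term and adds two. The article describes pre-treatment severity as an important indicator of treatment response and says the site-specific team may matter for outcomes. Site and stimulability could therefore recover some or all of what clinician removed; Step 5 shows that the amount needed is not implausible. Site also captures any difference between the two teams, and standard training and fidelity checks are meant to keep clinicians alike. The pilot clinician effect comes from only 23 children and may not carry over.

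All of this stands as far as the size of the loss is concerned. It does not remove the mismatch. Site can absorb only differences between sites, and the article does not say how many clinicians work at each. Nothing in the article shows that the planned covariates give an SD of 18.

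A reader might also draw four stronger conclusions that the article does not support.

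- *That the interval will be wider and power lower.* The clinician share is unreported and two terms are added, so this is possible but not shown.
- *That the residual SD must lie between 18 and 24.3.* Neither end is a bound. The added terms could take it below 18, and 24.3 would require all three planned covariates to explain nothing.
- *That the whole gap between 80% and the power under the stated decision rule is due to clinician.* The rule reads "If the lower bound of the 95% confidence interval centered on the observed difference falls above the noninferiority margin of -10.4 in both models", which corresponds to one-sided 2.5% if the interval is two-sided. At SD 18 that alone takes power from 80% to 70%, and it is a separate issue.
- *That chance imbalance of clinicians between arms biases the estimate.* Under randomization it is not bias. Its variance is already part of the residual SD and should not be counted twice.

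**Conclusion.** The concern holds as a mismatch between the planning SD and the planned primary model. The stated 80% power rests on an SD conditional on clinician, and the model that decides non-inferiority does not condition on clinician. The inconsistency is certain from the text; its consequence is not. Power is below plan to the extent that clinician explains variance beyond site, stimulability and baseline accuracy, which could be nothing or could be several percentage points or more. Residual SDs of 20 and 22 correspond to losses of about 7 and 15 points from 80%; the fall to 58% at the raw SD is an extreme, not an expected result.

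These figures assume 38 analysed per group, a true difference of 0, the margin of 10.4 and one-sided 5%, the settings that reproduce the plan's own number. The point should be put right but does not invalidate the design.

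**What to change.** Before any outcome data are seen, do one of the following.

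1. **Add treating clinician to the primary model**, in both the intention-to-treat and the per-protocol fits. Use either a random intercept or a fixed effect that replaces site, on the understanding that each clinician works at one site. First confirm that clinicians treat children in both arms. If they are largely specific to one arm, a clinician term would be confounded with treatment and would inflate the variance of the group difference. With few clinicians a random intercept would also be poorly estimated. Where the condition is met, the cost is a few of about 71 degrees of freedom and no new data, since the secondary survey model already needs clinician.
2. **Keep the primary model as written.** Refit the 23-participant data with those planned covariates that are available there, report the resulting SD, and restate the power for 38 per group. The cost is one refit of existing data and a revised sentence. The new SD will still be imprecise, so a range of power is more honest than a single figure.

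In either case, state which covariates the planning SD reflects, so that it can be matched to the model.
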